### Randomization and allocation concealment

Participants of each community health center will be randomized 1:1 within center into a couple-based arm (intervention) and an individual-based arm (control). To better balance key covariates, stratified randomization by patients’ gender and age group will be performed by a statistician otherwise not involved in the project using STATA 15. The order of which arm receiving each education session first will also be randomized, to ensure that the treatment sequence is equivalent between arms. Other than the statistician, all the research staff and community health workers will not know the group allocation prior to the education session. The community health workers designated as the care managers will call the participants to inform them of their group allocation, and to schedule the first session.

### Procedures

As outlined in Table 1, the intervention and control arms will take four-weekly group education & training sessions, and receive behavior change booster calls over the following 2 months. The education content will mainly be based on the T2DM management program [31] covering the topics of diabetes and complications, healthy diet, medication and exercise; and embody behavior change techniques (BCTs) [32]. During the intervention, patients will maintain their routine treatment. Interventions are targeted at both the patients and their spouses for the intervention arm, while only at the patients for the control arm.

**Table 1 Tab1:** Intervention components for intervention and control arms

Module	Dosage & Delivery	Components	Couple-based Intervention Group	Individual-based Control Group	BCT ^**a**^
**Health Education & Training**	4 weekly 2-h sessions, delivered by two care managers in class.	**Group Education**	T2DM patients & their spouses	T2DM patients	Comparison of behavior
		**1. Diabetes** & **Complication**			
		Understand diabetes Hypoglycemia Glucose monitoring	Couple-level discussion & practice	Patient-level discussion & practice	Shaping knowledge
		**2. Healthy Diet**			
		Diabetes nutrition Food label Dietary plan	Collaborative- management Collective behavior goal setting	Self-management Individual behavior goal setting	Social support ^b^ Goals & planning
		**3. Medication**			
		Taking (multi-) medication Medication adherence Foot care	Couples identify barriers & solutions collaboratively;	Patients identify barriers & solutions themselves;	Antecedents Association
		**4. Being Active**			
		Exercise recommendations Risk management Exercise goal & plan	Use “we will” in these activities.	Use “I will” in these activities.	Goals & planning
**Behavior Change Booster**	2 months of weekly tailored call	Interactive call tailored to participant’s behavior change barriers, with call frequency varied by their progress.	Deliver to the couple	Deliver to the patient only	Repetition & substitution Feedback & monitoring
**Behavior Change Incentive**	Throughout intervention	Vouchers gain or lose by fulfilling or failing management tasks, with group ranking.	Incentives for individual & couple performance	Incentives for individual performance only	Reward & threat

^a^ BCT: behavior change technique was defined by Behavior Change Techniques Taxonomy Volume 1 [30]

^b^ BCT for couple-based intervention only

### Interventions

#### The individual-based education & training

The four weekly two-hour structured group-education sessions focusing on T2DM management will be attended by eight to ten patients and facilitated by two care managers. The patients’ spouses, other family members or friends will not participate in these sessions. Discussion and practice will be organized to reflect patients’ own health and daily management issues. At the end of each session, patients will set a health-related behavior goal (e.g. exercise three times over the next week) and will report their progress in the next session with the group. Primary BCTs utilizes are social comparison, sharping knowledge, natural consequences, and goals and planning.

#### The couple-based education & training

The couple-based education groups consist of eight to ten couples (patients and their spouses) and two care managers. The education and training components will be framed as the couple’s issues whenever possible, and couple-level discussions and practices are interspersed throughout the sessions. The couples are encouraged to share their pragmatic aspects of coping with T2DM, and care managers will provide knowledge and techniques on how spouses can aid the management process accordingly.

At the end of each session, couples will set health-related behavior goals and make plans for the following week, which will be reviewed among the group at the beginning of the next session. They will be instructed to make these plans following the collaborative implementation intentions [30], that is the joint self-regulatory strategies involving both partners in planning when and where to perform a specific behavior task. Couples will set their personalized behavior goals, and make plans regarding when, where and how to achieve those goals collaboratively. Specifically, they are encouraged to list potential barriers in achieving these goals and identifying the best ways for the partner to help each other overcome these barriers. Spouses are instructed to set goals facilitative to their partners’ goals whenever possible (Additional file 2. Example for physical activity plan & goal).

The care managers serve as a resource to facilitate discussion within and between couples, and to instruct patients and their spouses to collaboratively make behavior plan. They are also trained to be aware of the spouses’ health condition, who are likely to have multiple chronic conditions themselves. In addition to the BCTs utilized in the individual-based education & training, couple-based education sessions further demonstrates restructuring the physical and social environment as antecedents of behavior change, as well as practical and emotional support from the closest person.

#### Behavior change booster

To reinforce and monitor participants’ progress in T2DM management, weekly booster calls will be delivered over the following 2 months. Given personalized messages with tailored feedback and frequency are more effective in promoting behavior changes [33], booster calls are designed to address participant’s behavior change barriers and call frequency are varied by participants’ progress. During the first call, trained investigators will examine the extent to which the patients have fulfilled behavior change action plans corresponding to the four education sessions, and provide motivational, informative and problem-solving feedbacks accordingly. Follow-up calls will be scheduled based on patients’ performance and only targeted at these behaviors that needs further attention. For example, if the patients fulfilled two out of the four behavior plans, the following week’s call will only address the other two unsolved behavior change tasks. If the patients have achieved all behavior change goals, they will only be contacted after another 3 weeks to review maintenance. While only the patients of the control arm will be contacted, both the patients and their spouses of the intervention arm will receive the call. Spouses are encouraged to review the couples’ progress jointly (e.g. healthy diet and exercise); and discuss ways to help the patients achieve the behavior change goals (e.g. glucose monitoring) and will receive suggestions from the investigators. BCTs associated with this module are repetition and substitution, as well as feedback and monitoring.

#### Behavior change incentives

To assist the delivery of the intervention, we further incorporate the reward and threat BCTs addressing both material and social incentives and rewards. Considering evidence from behavioral economics, incentives are designed to leverage the persons’ loss aversion [34] and social influences [35]. Participants of both arms will be given same amount of virtual vouchers upon enrollment. They can win extra vouchers by attending education sessions and fulfilling management tasks; or lose these vouchers vice versa. In the individual-based control arm, gain or loss depends on the patient own behavior only. In contrast, for the couple-based intervention arm, participants’ gain or loss not only depends on their own behavior, but also on the collaboration of the couples, meaning that the award or penalty will be doubled if both of them complete or fail the task. The total number of vouchers will be ranked and announced within their education group; which can be used to redeem gifts at the end of the course.

#### Intervention fidelity

The interventions of both arms will be delivered by two community health workers of each selected health care center. These designated care managers will receive ten-hour training of the interventions prior to the first group education session, and will be supervised by the research team while implementing the interventions. To maintain the fidelity of the intervention delivery, care managers will follow the manualized interventions, and take a structured fieldnote questionnaire (e.g. length of each session, any interruptions, participant dynamic and mood etc.). The educational sessions will be taped and monitored. In addition, participants’ attendance rates for each session and reasons for non-attendance will be collected for the implementation evaluation.

#### Study measures

Patients and their spouses will complete the baseline questionnaire and physical examination. Follow-up assessments are at 3 (immediately after intervention), 6, and 12 months after baseline (Table 2). Research assistances will conduct the two assessments on behavioral and management efficacy for both arms at 3 and 6 months via telephone. Patients of both arms will maintain their routine doctor appointments scheduled at the 6-month follow-up when their venous blood sample will be collected. Following the standard requirements for blood transportation, the blood sample will be mailed to Daan Gene, a university-affiliated clinical laboratory for examination. The endpoint in-person assessment at the 12-month will be conducted at community health care centers for all participants. All data obtained will be double entered into and managed by the Research Electronic Data Capture (REDCap) system [36, 37] hosted at hosted at Sun Yat-sen Global Health Institute. Outcome assessors will be blinded to the group assignments and will be different from care managers who conduct and monitor the interventions. Data analysts will remain blinded to the group assignment throughout the study.

**Table 2 Tab2:** Schedule of enrolment, interventions, and assessments

		STUDY PERIOD					
	Enrolment	Baseline Assessment	Allocation	Intervention	Follow-up		
**TIMEPOINT** (T for Month)	**T**_**−2**_	**T**_**−1**_	**T**_**0**_	**T**_**1–3**_	At end of **T**_**3**_	At end of **T**_**6**_	At end of **T**_**12**_
**ENROLMENT:**							
Eligibility screen	X						
Informed consent	X						
**ALLOCATION**			X				
**INTERVENTION:**							
Couple-based Intervention Group				X			
Individual-based Control Group				X			
**ASSESSMENTS AND MEASUREMENT:**							
Baseline socio-demographics: **age, gender, marital status, education, retirement status**, etc.	X						
Mental health: **C-MMSE**, **CES-D**		X					
***Primary outcomes:***							
Blood glucose ^a^: **HbA**_**1c**_		X				X	X
Quality of life: **SF-36**		X				X	X
***Secondary outcomes:***							
Metabolic measures: **BP, BMI, WHR, FG & lipid**		X					X
Management behaviours ^a^: **SDSCA**		X			X	X	X
Medication adherence ^a^: **BMQ & medical records**		X			X	X	X
Physical activity ^b^: **IPAQ-C**		X			X	X	X
Dietary ^b:^**FFQ**		X				X	X
***Process measures:***							
Management efficacy ^b^: **C-DMSES**		X			X	X	X
Dyadic appraisal & coping ^b^: **Communal coping** & s**upport**		X			X	X	X

*C-MMSE* Chinese Mini-Mental State Examination, *CES-D* the Centre for Epidemiologic Studies Depression Scale, *HbA1c* hemoglobin A_1c_, *SF-36* 36-item short form survey, *BP* blood pressure, *BMI* body mass index, *WHR* waist hip ratio, *FG* fasting glucose, *SDSCA* summary of diabetes self-care activities, *BMQ* brief medication questionnaire, *IPAQ-C* International Physical Activity Questionnaire-Chinese, *FFQ* food frequency questionnaire, *C-DMSES* the Chinese version of the Diabetes Management Self-efficacy Scale

^a^ Measure for patients only

^b^ Repeat measure for spouses of the control arm only at baseline and 12 months

#### Primary outcomes

The primary outcome for the patients is glycemic control, as measured by mean changes in HbA_1c_ levels over the 12-month follow-up. HbA_1c_ is an indicator of average blood glucose over the past 2 to 3 months [24].

For the spouses, health-related quality of life as measured by the 36-item Short Form Survey (SF-36) [38] is selected as the primary outcome. SF-36 covers physical functional health and well-being scores and has been validated among Chinese older adults [39]. Patients will also take the SF-36 survey as one of their secondary outcomes.

#### Secondary outcomes

Metabolic outcomes for both the patients and their spouses include waist/hip ratio, body mass index (BMI), blood pressure, fasting glucose and lipid profile.

Patients’ diabetes management behaviors will be assessed by the Summary of Diabetes Self-Care Activities (SDSCA) questionnaire [40]. SDSCA has 12 items evaluating the number of days in the past week that patients perform exercise, healthy diet, glucose monitoring, foot care, and medication adherence. The more days they conduct these self-care activities as required, the higher the score will be. The SDSCA has been validated among Chinese T2DM patients [41]. Medical adherence will be assessed by medical record and the brief medical questionnaire [42], screening patient adherence and barriers to adherence.

Physical activity behavior will be measured by the International Physical Activity Questionnaire (IPAQ)-Short Form [43], which evaluates the frequency and duration of four types of physical activities over the past week. The validity and reliability of IPAQ-Chinese has been previously established among older Mainland Chinese [44]. Dietary will be evaluated by the food frequency questionnaire customized to the Chinese Chronic Non-Communicable Diseases and Risk Factor Surveillance questionnaire [45, 46], to assess food intake and changes in eating behaviors over the past 6 months. These two behavior measures will be applied to patients and spouses.

#### Process measures

Management efficacy will be examined by the Chinese version of the Diabetes Management Self-efficacy Scale (C-DMSES) [47]. The 20-item C-DMSES assesses patients’ confidence in conducting diabetes management daily activities from 0 (can’t do at all) to 10 (certain can do). Spouses will also evaluate their confidence in assisting the patients completing these activities on the same 11-point scale [48].

Couples’ dyadic appraisal and dyadic coping behaviors of diabetes will be examined by questionnaires synthesized by Helgeson et al., 2019 [49]. Patients and their spouses will individually evaluate whether they think diabetes is an individual or shared problem (dyadic appraisal) [50], and the extent to which they had engaged in collaborative supportive and unsupportive activities during the past month on a five-point Likert scale from 1 (not at all) to 5 (very often) (dyadic coping).

#### Statistical considerations

Descriptive analyses comparing couples’ baseline characteristics between the intervention and control arms will be performed to assess the balancing of the group assignment. The intention-to-treat (ITT) approach will be applied to examine the treatment effects in accordance with the original randomization assignments. Missing baseline covariates and missing outcomes will be multiply imputed under missing at random assumption and separately by treatment arms [51].

The multilevel linear mixed modeling (MLM) will be employed to evaluate repeat measures of participants over time, while accounting for variations between community health care centers (blocks). The longitudinal changes of patients’ HbA_1c_ within- and between- treatment arms over 12 months will be examined, and the treatment effect is estimated as the differences between the within-arm changes from baseline to follow-up between the two intervention arms. MLM will be also applied to other continuous outcomes with one or more repeat measures, adjusted for time, study arm, a time and study arm interaction, and baseline covariates. The treatment effect will be further examined in two subgroup analyses, stratified by gender and patients’ baseline glycemic levels. All analyses will adjust for baseline sociodemographic covariates and functional states that are statistically-significantly different between treatment arms, and empirically-suggested as strong predictors for the outcomes.

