### Sample size

The sample size calculation was based on the primary hypothesis that the couple-based intervention would result in a 0.5% more reduction in HbA_1c_ as compared to the individual-based intervention over 12 months. This difference in HbA_1c_ is interpreted as a clinically meaningful change in glycemic control [23, 24]. A sample size of 194 couples (97 couples per arm) would provide 80% power to detect a between-arm difference of this magnitude (standard deviation (SD) =1.5%) for a longitudinal design with three repeated measures having an autoregressive covariance pattern, assuming the correlation between observations on the same subject of 0.5 [25], *α* of 0.05, and a 10% dropout rate.

The proposed sample size also satisfies the power requirement for subgroup analyses among male patients and patients with baseline HbA_1c_ ≥ 8.0%. These two subgroup analyses were chosen, considering the traditional female-dominated role in meal preparation and caregiving [26]; and a more evident reduction in HbA_1c_ among those with worse baseline glycemic control [20]. In light of previous couple-based T2DM interventions [20, 27, 28], it is assumed the ratio of male vs female patients enrolled would be around 1.2, resulting in 106 male participants available for subgroup analysis. With *α* of 0.05 and an auto-correlation of 0.5, the study will have over 90% power to detect a between-arm difference of 0.6% in HbA_1c_ (SD = 1.1%). Similarly, for the subgroup of patients with HbA_1c_ ≥ 8.0% (assuming *n* = 64, 33% of the whole sample), our study will have 90% power to detect a between-arm difference of 0.7% in HbA_1c_ (SD = 1.1%). Sample size and power calculation were conducted by PASS 11, using two independent means with repeated measures procedure [29] .

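### Both arms are taught in education groups of 8 to 10, but neither the stated model nor the sample size allows for correlation within those groups

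*Protocol article*

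**What the plan says.** Under Randomization and allocation concealment, couples are allocated 1:1 within each community health center. Delivery is then by group in both arms:

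- Control sessions "will be attended by eight to ten patients and facilitated by two care managers", and control patients "will report their progress in the next session with the group".
- For the intervention arm, "The couple-based education groups consist of eight to ten couples". Couples' goals and plans are likewise reviewed in the group at the next session.
- Under Behavior change incentives, for both arms: "The total number of vouchers will be ranked and announced within their education group".
- Under Intervention fidelity: "The interventions of both arms will be delivered by two community health workers of each selected health care center".

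The Statistical considerations section specifies a multilevel linear mixed model for repeated measures, "accounting for variations between community health care centers (blocks". The treatment effect is the between-arm difference in change from baseline. No term for education group, or for centre by arm, is mentioned.

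The Sample size section states: "A sample size of 194 couples (97 couples per arm) would provide 80% power". Its inputs are a 0.5% difference in HbA1c, SD 1.5%, three repeated measures with an autoregressive pattern and correlation 0.5, α 0.05 and 10% dropout. No ICC, group size or design effect appears.

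**The concern.** This is an individually randomised trial with group-delivered treatment. Members of a group share sessions, hear each other's progress and are ranked against each other, so their later outcomes may be correlated even though they were randomised one couple at a time.

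The centre term does not deal with this. Each centre contributes to both arms, so whatever is common to a centre drops out of the within-centre comparison of arms. An education group belongs to one arm only, so the variance between groups passes straight into the estimated treatment difference. A model with participant and centre levels treats that variance as if it averaged out over individuals.

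At stake are the error rate of the primary HbA1c test, the width of the between-arm intervals from the same model, and the credibility of the stated 80% power.

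**Working it through.** **1. Reproduce the planned sample size.** All inputs are from the Sample size section.

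- Variance factor for the mean of three first-order autoregressive measures with correlation 0.5: (3 + 2 × (0.5 + 0.5 + 0.25)) / 9 = 0.6111.
- Variance of that mean: 1.5² × 0.6111 = 1.375 (SD 1.173).
- Evaluable per arm for 80% power, two-sided α 0.05: (1.960 + 0.842)² × 2 × 1.375 / 0.5² = 86.3, rounded up to 87.
- With 10% dropout: 87 / 0.9 = 96.7, so 97 per arm and 194 in total. This matches the article.
- Power at 87 per arm: standard error = √(2 × 1.375 / 87) = 0.1778; 0.5 / 0.1778 = 2.812; Φ(2.812 − 1.960) = 80.3%.

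The article does not state sidedness; two-sided reproduces the figure. There is no hidden allowance for groups and almost no slack.

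**2. Add a group correlation.** With group size m, the design effect is DE = 1 + (m − 1) × ICC. Then:

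- power = Φ(0.5 / √(2 × 1.375 × DE / 87) − 1.960)
- type I error if groups are ignored = 2 × (1 − Φ(1.960 / √DE))
- enrolment for 80% power: 86.3 × DE per arm rounded up, then divided by 0.9 and rounded up

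The ICC values are assumed, since the article gives none. With m = 9:

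| Assumed ICC | DE | Power | Type I error if ignored | Total enrolment for 80% power |
|---|---|---|---|---|
| 0 | 1.00 | 80.3% | 5.0% | 194 |
| 0.01 | 1.08 | 77% | 5.9% | 210 |
| 0.02 | 1.16 | 74% | 6.9% | 226 |
| 0.05 | 1.40 | 66% | 9.8% | 270 |
| 0.10 | 1.80 | 55% | 14.4% | 348 |

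Worked line for ICC 0.05: √(2 × 1.375 × 1.40 / 87) = 0.2104; 0.5 / 0.2104 = 2.377; Φ(0.417) = 66%.

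Across groups of 8 to 10, power is 78–77% at ICC 0.01, 75–74% at 0.02, 68–65% at 0.05 and 58–53% at 0.10.

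**3. Separate the cost of having few groups.** With 97 couples per arm there are about 97/10 to 97/8, that is 10 to 12, groups per arm. A correct analysis uses a t reference tied to the number of groups. For m = 9 the degrees of freedom are about 2 × 97/9 − 2 = 19.6. Step 2's power then becomes 76% at ICC 0, 73% at 0.01, 70% at 0.02, 62% at 0.05 and 51% at 0.10. The drop from 80% to 76% at ICC 0 is purely lost degrees of freedom, not clustering.

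The layout matters. With 11 centres, one group of 8 per arm in each (an assumption; the article mentions 11 districts but gives no number of centres or groups), a paired comparison of group means has 10 degrees of freedom and about 72% power even at ICC 0.

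**4. Limits of the approximation.** It applies one design effect to the mean of three measures, whereas the planned contrast is a change from baseline in a mixed model. Baseline HbA1c is measured before groups exist, so the group correlation can act only on follow-up values. The figures show scale; they are not the exact operating characteristics of the planned test.

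**The case against.** The strongest reply is that the residual group correlation may be small, and the article gives good reasons for that. The same two care managers deliver both arms in a centre from manuals, with sessions taped and monitored, so main facilitator effects fall largely into the centre effect. The two months of booster calls go to the patient or couple, not to the group. Group exposure is four two-hour sessions, and patients keep their routine treatment. HbA1c is a laboratory value taken at 6 and 12 months. What remains is mainly peer and session variance. All of this stands: nothing in the article points to an ICC of 0.05 or 0.10, and at 0.01 the loss is only about 3 points of power and 1 point of type I error.

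A second reply is that one condensed paragraph naming a multilevel model need not list every random effect. That is fair for the model: the absence of a group term is read from the one clustering level that is named. It does not help the sample size, whose inputs are given in full and leave no room for group clustering.

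A reader might infer that the primary test's type I error is certainly above 5%, or that 80% power is lost under any positive correlation. The documents do not support the first as fact, because they give no ICC. The second is almost literally true, since with groups of 9 the slack is used up at an ICC of about (87/86.3 − 1)/8 = 0.001, but it misleads because the loss at such values is negligible.

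**Conclusion.** The point holds conditionally. The design creates arm-specific groups, the stated model names only centre, and the stated power has no allowance for groups. For any positive group ICC beyond centre, the direction is certain: intervals too narrow, type I error above 5%, power below 80%. The size rests on an ICC that the article does not give.

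Over an assumed range of 0.01 to 0.10 with groups of 9, power runs from about 77% down to 55% and type I error from about 6% up to 14%. The design features above make the lower part of that range the more plausible. The upper figures should not be read as a forecast. Nor should power figures from a group-level analysis be read as the effect of clustering alone, because part of the fall comes from the small number of groups.

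The plan in effect assumes an ICC of exactly zero for an intervention that works partly through the group. That is worth correcting before recruitment, which the article had still to come.

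**What to change.** 1. Record an education-group identifier for every couple in REDCap.
2. Add a random effect for education group to the primary and secondary mixed models; use centre by arm if there is one group per arm in each centre. It must act on follow-up values or on change. A group intercept shared by baseline and follow-up would cancel from the change-from-baseline contrast and leave the problem in place.
3. Use small-sample degrees of freedom, given roughly 10 to 12 groups per arm.
4. For spouse outcomes, let the group variance differ by arm, because control-arm spouses do not attend the sessions.
5. Restate power in the Sample size section for groups of 8 to 10 over a stated ICC range, showing separately the loss from clustering and the loss from few groups.

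The cost is one data field, one random term and a revised paragraph. Intervals will be somewhat wider and the stated power less favourable. No extra patients are needed for the corrected analysis, but the correction does not restore 80% power.

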## Methods

### Study design

The study is a community-based multicenter, two-arm RCT. To control for variations within community health centers, a randomized block design is adopted with couples recruited at each center (block) randomly assigned to the couple-based intervention arm or the individual-based control arm (Fig. 2). The study was approved by the Sun Yat-sen University Institutional Review Board (Approval no. 2019–064). The protocol was developed and guided by the SPIRIT checklist (Additional file 1).

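### As written, baseline covariates cancel from the time-by-arm HbA1c estimate, and not conditioning on baseline HbA1c gives up precision that costs nothing to recover

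*Protocol article*

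**What the plan says.** Under Statistical considerations, for HbA1c, "the treatment effect is estimated as the differences between the within-arm changes from baseline to follow-up between the two intervention arms". The next sentence extends the same mixed model to the other continuous outcomes and lists its terms: "adjusted for time, study arm, a time and study arm interaction, and baseline covariates". The section's last sentence applies covariate adjustment to every analysis. It covers sociodemographic and functional-status variables that differ significantly between arms or are known strong predictors. No covariate-by-time or centre-by-time term is named.

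The same section says that missing covariates and outcomes are multiply imputed within arm, and that variation between centres is accounted for. On centre, the Study design section says: "To control for variations within community health centers, a randomized block design is adopted".

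Table 2 schedules HbA1c at baseline, 6 and 12 months. This matches the Sample size section, which assumes "three repeated measures having an autoregressive covariance pattern".

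**The concern.** Baseline HbA1c appears to be a response in the model. A covariate that is constant over time, entered without a time interaction, raises or lowers all of a patient's values by the same amount, so it says nothing about change. The trial's effect is a difference in change.

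Two things are at stake:

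- A result reported as adjusted would carry the same point estimate as the unadjusted one. Chance imbalance in a factor that predicts change would stay in it in full.
- Baseline HbA1c, already collected and likely to be the strongest predictor of later HbA1c, is used only by subtraction. That is less efficient than conditioning on it.

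**Working it through.** **1. Inputs (Sample size section).** The difference is "0.5% more reduction in HbA_1c_ as compared to the individual-based intervention over 12 months". The SD is 1.5%, with an autoregressive pattern and a "correlation between observations on the same subject of 0.5". Alpha is 0.05 (two-sided assumed), dropout 10%, power 80%, 97 per arm.

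**2. Reproducing the stated size.** The variance factor for the mean of three AR(1) measures is (3 + 4×0.5 + 2×0.25)/9 = 0.6111. Then n = 2 × (1.960 + 0.842)² × 1.5² × 0.6111 / 0.5² = 86.3, so 87 per arm. 87/0.90 = 96.7, so 97 per arm and 194 in total. The figure reproduces, but as a comparison of the average of three measures, not of a change from baseline.

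**3. Is baseline a response?** Three HbA1c measurements exist only if baseline is counted. The model is also applied to outcomes with a single repeat measure. In Table 2 the metabolic outcomes are taken at baseline and 12 months only, so a time-by-arm term for them needs baseline among the responses.

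**4. The cancellation.** Let x be a baseline covariate with coefficient g, and let the arm-by-time means be saturated. With complete data and a common within-patient covariance, the fitted arm difference at time t is

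b(t) = Ybar1(t) − Ybar0(t) − g × (xbar1 − xbar0).

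The last term does not depend on t, so b(t) − b(0) does not contain g. It equals the raw difference in mean changes. A constant centre term drops out in the same way. Multiple imputation makes each analysed data set complete, so the result is exact there.

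**5. Numerical check.** Simulated trials had 194 patients, 10 centres and a covariate deliberately imbalanced by arm that predicts change. The 12-month time-by-arm estimates were:

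| Simulated trial | Unadjusted | Covariates and centre as main effects | Covariate-by-time added |
|---|---|---|---|
| 1 | −0.16104 | −0.16104 | −0.41515 |
| 2 | −0.36231 | −0.36231 | −0.51137 |

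The estimates were the same under random-intercept, AR(1) and unstructured covariance. In trial 1 the SE was unchanged by main-effect adjustment under random-intercept (0.169) and unstructured covariance (0.195). Under re-estimated AR(1) it moved from 0.203 to 0.186. Where dropout was simulated and left unimputed, main-effect adjustment moved the estimate by 0.002 to 0.035.

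**6. Precision from baseline HbA1c (a separate matter).** With AR(1) 0.5, the correlation is 0.5 from baseline to month 6 and 0.25 from baseline to month 12. In units of SD²:

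- Mean of months 6 and 12: variance (1 + 1 + 2×0.5)/4 = 0.75; covariance with baseline (0.5 + 0.25)/2 = 0.375.
- Averaged change: 0.75 + 1 − 2×0.375 = 1.000. With baseline as covariate: 0.75 − 0.375² = 0.609.
- 12-month change: 2 − 2×0.25 = 1.5. With baseline as covariate: 1 − 0.25² = 0.9375.

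SE = 1.5 × √(2f/87), where f is the variance factor; power = Φ(0.5/SE − 1.96). The article's wording fits either contrast, so both are shown.

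| Contrast | Change: SE, power | Baseline as covariate: SE, power |
|---|---|---|
| Averaged follow-up | 0.227, 59% | 0.178, 80% |
| 12 months | 0.279, 43% | 0.220, 62% |

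**7. Range.** The gain depends on the correlation. For an assumed baseline-to-12-month correlation of 0.5, 12-month power is 59% against 72%; for 0.7, 81% against 87%. For the averaged contrast, an assumed AR(1) of 0.7 gives 77% against 88%, and 0.8 gives 90% against 94%.

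**The case against.** The strongest reply is that the article never says covariates enter as main effects only. Interaction terms are detail that a condensed article may leave to an analysis plan, and the term list formally introduces the other outcomes. This stands in part: the form is inferred. But the list names one interaction, the model is said to apply to these outcomes as well as HbA1c, and the adjustment covers all analyses. Main effects only is the most natural reading. Primary outcomes speaks of mean changes in HbA1c, so change scores could be the response. Main-effect covariates would then not cancel. The three repeated measures and the single-repeat outcomes argue against that reading, without excluding it.

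A reader might infer more than the documents support:

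- **That the effect would be biased.** It would not. Under 1:1 randomization the difference in mean changes is unbiased. What is lost is correction of chance imbalance, and stratifying by gender and age group already limits imbalance in those two.
- **That control for centre is lost.** Differencing removes stable centre levels, and allocation is balanced within centre. Only centre differences in change remain.
- **That adjustment alters nothing in the report.** The SE, and so the p-value, can move under AR(1). Covariates could also act through the imputation model, although that is not the stated adjustment.
- **That the cancellation causes the power loss.** The 59% against 80% comes from how baseline HbA1c is used. The planned covariates are described as sociodemographic and functional, so this is a second, separate point.

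**Conclusion.** The point holds in a limited form. If covariates enter as written, then on the imputed data they have no effect on the time-by-arm point estimate, and the promised adjustment cannot correct chance imbalance in predictors of change. The estimate remains valid, so this does not invalidate the trial.

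The precision loss does not depend on how the other covariates enter, but it assumes that the analysis does not condition on baseline HbA1c. On the plan's own assumptions it is about 21 percentage points of power for the averaged contrast and 19 at 12 months. At an assumed 12-month correlation of 0.7 it shrinks to about 6 points. These are normal approximations with 87 completers per arm and a two-sided test. The point is best treated as a free improvement: a better use of data already being collected.

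**What to change.** State in the analysis section that month-6 and month-12 HbA1c are the responses. The fixed effects are arm, visit, arm-by-visit, baseline HbA1c, baseline-by-visit, centre, gender and age group, with an unstructured within-patient covariance. A constrained longitudinal model with a common baseline mean in both arms and covariate-by-visit terms serves the same purpose and may be preferred if baseline is to stay among the responses.

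Use the same form for SF-36 and the other continuous outcomes. For those with one follow-up value it reduces to analysis of covariance on the baseline value. If a full analysis plan already contains such terms, bring the article's wording into line with it.

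The cost is a change in analysis wording. It needs no new data, patients or visits, and the Trial status section shows that recruitment had not begun when the article was written.
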